Appendix I)

1.0 HYPOTHESES AND STUDY OBJECTIVES

## 1.1 Hypotheses

1.1.1 In treatment-naïve subjects starting a potent ARV regimen consisting of RAL and FTC/TDF, plasma HIV-1 RNA levels will exhibit steeper declines over the first 14 days of treatment compared to the declines previously seen in subjects receiving the efavirenz (EFV)-based three-drug combinations used in the A5160s and A5166s protocols.

1.1.2 Subjects with more rapid first-phase decay (larger d1) will exhibit poorer CD4+ T-cell restoration, as evidenced by: (a) smaller increases from baseline in CD4+ T-cell counts on day 14, and (b) smaller increases from baseline in CD4+ T-cell counts at week 24.

1.1.3 Subjects with more rapid turnover of central memory T-cells at baseline, will exhibit poorer CD4+ T-cell restoration, as evidenced by: (a) smaller increases from baseline in CD4+ T-cell counts on day 14, and (b) smaller increases from baseline in CD4+ T-cell counts at week 24. Speed of turnover of central memory T-cells will be represented by the proportion of CD45RA-/CD27+ cells (CD4+ or CD8+) that: (c) are in cell cycle (Ki-67+) and/or (d) express one or both activation markers CD38, HLA-DR, as measured at baseline.

1.1.4 The rate of absolute change (slope) in proportions of activated central memory (CM) (CD45RA-CD27+) CD4+ and CD8+ T-cells between baseline and inflection point will correlate inversely with the magnitude of CM and total CD4+ T-cell restoration at day 14 and week 24.

1.1.5 Subjects with more rapid first-phase decay will exhibit more rapid turnover (as manifested by proportions of Ki-67+ cells) of CM T-cells at baseline.

1.1.6 Baseline levels of bacterial 16s DNAs that are reflective of the damaged gut mucosal barrier to translocation will correlate with the baseline proportions of activated CM T-cells.

1.1.7 Baseline plasma HIV-1 RNA levels will correlate with baseline proportions of activated CM T-cells.

1.1.8 A mathematical model that takes into account both plasma levels of HIV-1 RNA and plasma levels of bacterial 16s DNAs will correlate better with baseline levels of immune activation and will predict better the magnitude of CD4+ T-cell restoration (inversely) than will either index alone.

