# 9.0 STATISTICAL CONSIDERATIONS

## 9.1 General Design Issues

This is a prospective, single-arm, 72-week pilot study to estimate the first-phase viral decay constant (d1) in treatment-naïve subjects initiating a three-drug regimen consisting of the HIV-1 integrase inhibitor RAL and NRTI combination FTC/TDF.

In general, analyses that address mechanisms of pathobiology will be conducted on subjects as treated (AT), and analyses of markers for clinical outcome will be ITT. The accrual target of 34 subjects is expected to yield plasma HIV-1 RNA data from 30 subjects for model-fitting, and thus provide a 95% CI around the estimated d1 of no wider than ±0.07, assuming the population mean and standard deviation of d1 for the study regimen are 0.80 and 0.20, respectively. Under these assumptions, with usable data from 30 subjects, there is 98% probability that the CI around the estimated d1 will exclude the value 0.65.

Subjects who modify the study regimen or miss doses are expected to stay on study and be followed; however, they will be replaced as follows: If the subject changes the regimen or misses any dose from day 0 through 14, an additional subject will be accrued. For every three subjects who change regimen or miss 2 or more doses from day 15 through 56, an additional subject will be accrued. (Although subjects dropping out before day 57 will be replaced in this way, the buffer of 4 additional subjects [Section 9.4] is retained to allow for missing results on obtained samples.) Such subjects will be excluded from AT analyses and included in ITT analyses. (See Section 9.6 for details.) From day 57 and thereafter, subjects altering the treatment regimen or missing doses will not be replaced; those who alter the regimen or miss more than 7 cumulative days of doses will be excluded from AT and included in ITT analyses.

The primary objective will be analyzed when plasma HIV-1 RNA results through day 28 are available (as quantified using the standard assay). Specifically, when the last subject to enroll has reached day 21, sites will be asked to send those batched plasma HIV-1 RNA samples that are intended for standard assay to the assay lab (Johns Hopkins University). When results for these samples and when the real-time results for the day 28 and 56 samples are available, analysis to estimate first and second phase viral decay rates will begin.

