For various combinations of sample size and SD of d1 estimates, Table 7 presents the resulting “plus-minus” amounts (half-widths) of 95% CIs. For example, if the population SD of d1 is 0.20, a sample size of 30 subjects (with usable data) will provide CI lower and upper bounds ± 0.07 around the mean. If the true SD(d1) is smaller than 0.20, CIs will be narrower. Assuming the population mean d1 for the study regimen is 0.80, Table 8 presents the probability that 95% CIs will lie entirely above the value 0.65. For example, if the population mean and SD of d1 are 0.80 and 0.20, respectively, and the sample size is 30 subjects with usable data, there is 98% probability that the 95% CI around the sample mean will exclude (and fall above) the value d1=0.65.

Approximately 14% of subjects who enrolled to A5166s had to be excluded from analysis due to drug interruptions. (HIV-1 RNA levels excluded for non-monotonicity were a subset of these.) To allow for such losses in the current study, a buffer of 4 additional subjects is added to the goal of 30 analysis-eligible subjects, bringing the accrual target to 34.

Table 6. Estimates of d1 and its standard deviation from similarly designed and analyzed viral dynamics studies.

| Study | Arm | Estimated  d1 | Estimated  SD(d1) |
| --- | --- | --- | --- |
| A5166s (A5095) | C: EFV + 3TC/ZDV (superior arm) | *0.67  **0.70 | *0.10  **0.18 |
|  | B: ABC + 3TC/ZDV | *0.56  **0.58 | *0.12  **0.06 |
|  | A: EFV + ABC + 3TC/ZDV | 0.59 | 0.08 |
| A5160s (A5142) | C: EFV + 2 NRTIs (superior arm) | 0.64 | 0.09 |
|  | A: EFV + LPV/r | 0.61 | 0.09 |
|  | B: LPV/r + 2 NRTIs | 0.53 | 0.18 |
| Móltó | ENF + EFV + LPV/r + 3TC + TDF | 0.80 | 0.13 |
|  | EFV + LPV/r + 3TC + TDF | 0.62 | 0.18 |

* From subject-specific estimates. ** From MCMC-based population estimates.

Table 7. Expected precision for d1 estimates for various combinations of sample size and underlying population standard deviations around true d1. Precision expressed as ± amounts (half-widths) for 95% CIs (assuming normality of d1).

| Sample size | Population standard deviation around d1 | | | | | |
| --- | --- | --- | --- | --- | --- | --- |
| 0.12 | 0.15 | 0.18 | 0.20 | 0.23 | 0.25 |
| 10 | 0.09 | 0.11 | 0.13 | 0.14 | 0.16 | 0.17 |
| 15 | 0.07 | 0.08 | 0.10 | 0.11 | 0.13 | 0.14 |
| 20 | 0.06 | 0.07 | 0.08 | 0.09 | 0.11 | 0.12 |
| 25 | 0.05 | 0.06 | 0.07 | 0.08 | 0.09 | 0.10 |
| 30 | 0.04 | 0.06 | 0.07 | 0.07 | 0.09 | 0.09 |

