The primary AT analysis will exclude endpoints corresponding to samples collected after an interruption or modification in the study regimen. The primary analysis will also include only those subjects for whom d1 could be estimated. Secondary analyses in which d1 is not a variable may include subjects without d1 estimates. Associations between the following pairs of variables will be examined, as described in the analysis plan: (1) baseline plasma HIV-1 RNA levels and baseline proportion of activated CM T-cells, (2) subject-specific d1 estimates and CD4+ T-cell increases (day 14, week 24; separate outcomes), (3) baseline CM T-cell turnover and CD4+ T-cell increases (day 14, week 24; separate outcomes), and (4) subject-specific d1 estimates and baseline CM T-cell turnover.

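### Section 9.6.2.12 requires an estimable d1 in the primary analysis of all four associations, although two do not involve d1 and one of these is purely pre-treatment

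*Protocol*

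**What the plan says.** Section 9.6.2.12 gives two rules for its primary analysis. The first acts on samples: "The primary AT analysis will exclude endpoints corresponding to samples collected after an interruption or modification in the study regimen". The second acts on subjects: "The primary analysis will also include only those subjects for whom d1 could be estimated". The second rule makes no distinction by pair. The next sentence shows that this is deliberate, since it admits the other subjects only elsewhere and only as an option: "Secondary analyses in which d1 is not a variable may include subjects without d1 estimates".

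Four pairs follow. Pairs (2) and (4) contain d1. The other two do not: "1) baseline plasma HIV-1 RNA levels and baseline proportion of activated CM T-cells" and "3) baseline CM T-cell turnover and CD4+ T-cell increases (day 14, week 24; separate outcomes". Pair (1) is the analysis of hypothesis 1.1.7: "Baseline plasma HIV-1 RNA levels will correlate with baseline proportions of activated CM T-cells". Pair (3) serves hypothesis 1.1.3.

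On numbers, section 9.1 says: "The accrual target of 34 subjects is expected to yield plasma HIV-1 RNA data from 30 subjects for model-fitting". Section 9.4 supports the allowance of four with an earlier substudy: "Approximately 14% of subjects who enrolled to A5166s had to be excluded from analysis due to drug interruptions". Section 9.6.2.12 gives no effect size, test, significance level or power, and no reason for the d1 condition.

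**The concern.** Both variables in pair (1) exist before treatment starts. Section 6.1 schedules plasma HIV-1 RNA and the advanced flow assay at pre-entry and entry, and section 6.2.2 requires the entry evaluations to be finished before study medication begins. Whether d1 can be estimated is settled later, by missed doses, regimen changes, rebound or missing RNA results over days 0 to 56. The condition therefore chooses the sample for a pre-treatment association by what happens after treatment starts. The general rule in section 9.1 that pathobiology analyses are as-treated does not call for this, because no treatment precedes these samples.

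For pair (3) the sample rule alone already removes CD4+ values taken after an interruption or modification. The d1 condition can only remove further subjects whose two values are sound.

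At stake are precision in a study of about 34 subjects and a clean reading of hypothesis 1.1.7. As written, the larger valid sample is optional and the needlessly selected one is primary.

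**Working it through.** **1. The plan's own figure.** The only stated probability that uses n = 30 is for mean d1 (sections 9.1 and 9.4: mean 0.80, SD 0.20, reference value 0.65, 98%, half-width 0.07). The half-width is t(0.975, 29) × 0.20/√30 = 0.0747. The noncentral t with noncentrality 0.15/(0.20/√30) = 4.11 gives 97.8%. Both agree with the plan, so 30 is the plan's working number with a usable d1. There is no corresponding figure for the associations.

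**2. Inputs for pair (1).** n = 30 with the d1 condition and n = 34 without it (sections 9.1 and 9.4). The true correlation r and the two-sided 5% level are assumptions. So is the premise that all 34 have both baseline values, which makes 34 an upper limit for the accrual target.

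**3. Precision, which needs no assumed r.** The 95% half-width on the Fisher z scale is 1.96/√(n − 3). This is 1.96/√27 = 0.377 at n = 30 and 1.96/√31 = 0.352 at n = 34. The ratio is √(27/31) = 0.933, so the interval is about 7% narrower.

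**4. Power.** Power = Φ(atanh(r)·√(n − 3) − 1.96) plus the small opposite tail. At r = 0.4, atanh(r) = 0.4236. For n = 30: 0.4236 × 5.196 − 1.96 = 0.241, giving 59.5%. For n = 34: 0.4236 × 5.568 − 1.96 = 0.399, giving 65.5%.

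| Assumed r | n = 30 | n = 34 | Difference (points) |
|---|---|---|---|
| 0.1 | 8.2% | 8.6% | 0.5 |
| 0.2 | 18.4% | 20.4% | 2.0 |
| 0.3 | 36.3% | 40.7% | 4.4 |
| 0.4 | 59.5% | 65.5% | 6.0 |
| 0.5 | 81.4% | 86.4% | 5.0 |
| 0.6 | 95.0% | 97.1% | 2.2 |
| 0.7 | 99.5% | 99.8% | 0.3 |

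Differences are taken before rounding. The maximum over all r is 6.0 points. If only 2 of the 34 lack d1 (n = 32 against 34), the maximum is 2.9.

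**5. Replacement.** Section 9.1 accrues replacements, so enrolment can exceed 34. An extreme scenario treats 14% of enrolees as replaced one for one (34/0.86 = 39.5, about 40), all of them without d1, with 4 more also lacking it. Then n = 30 against 40 gives at most 13.6 points, at r = 0.4.

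**6. Pair (3).** A subject uninterrupted to day 14 has scheduled RNA samples on days 0, 2, 7, 10 and 14. One uninterrupted to week 24 has them through day 56. Such subjects would normally have a d1 estimate. Lifting the condition while keeping the sample rule therefore recovers mainly subjects with missing RNA results or early rebound. The table does not apply to this pair.

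**The case against.** The strongest defence has three parts.

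- **The case is provided for.** The protocol allows secondary analyses with these subjects, so the data need not be lost. The objective is the joint relationship of d1, activation and CD4+ restoration, and one common set keeps the four associations comparable. This stands in part. It is a real benefit, though not one the protocol states, and a sensitivity analysis in the d1-estimable set would keep it. It does not explain why a baseline association should be primary in that set.

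- **Few subjects may be affected.** Section 9.6.1 drops only RNA values collected after an interruption and keeps earlier ones, and subject-specific d1 values are empirical Bayes estimates, which partial data can support. Some interrupters may therefore have a d1. Section 9.1, however, excludes replaced subjects from as-treated analyses. The two sections leave the number unclear, and it may be below four. This stands and limits the size of the point.

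- **Not every baseline value will exist.** Section 9.1 keeps the buffer for missing results, and the flow assay needs enough viable cells. This also stands. Valid pair (1) data for every enrolled subject cannot be taken for granted.

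A reader might infer a power loss of up to about 14 points. The documents do not support that as an estimate. Section 9.1 replaces one for one only through day 14 and one for three from day 15 to 56. Section 9.4 does not split the 14% by period and already uses it to justify the four-subject buffer. Section 9.6.1 keeps pre-event data.

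**Conclusion.** The point holds as a minor one. The d1 condition has no function for pairs (1) and (3). For pair (1) it drops valid pre-dose data and selects on post-baseline events. The documents do not show how large any resulting bias would be or in which direction.

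On the plan's counts of 34 and 30 the cost for pair (1) is about 0 to 6 points of power, or an interval about 7% wider than it need be (0.377 against 0.352). The power range assumes two-sided 5%, a Fisher z test, and both baseline values in all 34. It is smaller if fewer than four lack d1 and larger if replaced subjects also lack it. For pair (3) the gain is small.

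Two stronger readings should be set aside. The restriction is not wholly without benefit, since it gives one common set. Nor does it exclude everyone who interrupts treatment, since the stated criterion is whether d1 could be estimated. This is a secondary objective of a pilot study, and the primary estimate of d1 is untouched.

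**What to change.** Change two sentences in section 9.6.2.12.

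- Apply the d1 condition to pairs (2) and (4) only.
- State the primary set for the other two. For pair (1), use all enrolled subjects with both baseline values, whatever their later adherence. For pair (3), use all subjects with baseline central memory turnover and a CD4+ count at the relevant time point (day 14 or week 24) taken before any interruption or modification, whether or not d1 was estimable.
- Keep the d1-estimable set as a sensitivity analysis for pairs (1) and (3).

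It would also help to reconcile sections 9.1 and 9.6.1 on whether replaced subjects can contribute a d1 estimate.

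No new samples or visits are needed, because the baseline samples are already scheduled for everyone. The one small cost is that the four pairs are no longer analysed primarily in one identical set.

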# 10.0 PHARMACOLOGY PLAN

## 10.1 Pharmacology Objectives

A5248 is a pilot study designed to examine viral decay rates in treatment-naïve subjects receiving RAL plus FTC/TDF. The primary pharmacology objective is to examine relationships between initial viral decay rates and RAL trough concentrations. Secondary objectives include examining relationships between RAL trough concentrations and later viral decay rates and the decay rate in unintegrated proviral DNA in PBMCs.

## 10.2 Study Design

Recent experience, additional PK data on RAL systemic exposure, and study design limitations limit the types of PK analyses that can be completed in this study. Due to the amount of samples being collected and the current inability to model RAL concentration-time data, we will only be collecting trough concentrations on subjects in the study. Each subject will have a single trough sample collected at each subsequent morning clinic visit post-entry. TDF and FTC concentrations will also be measured. A total of 3 mL whole blood should be collected for each trough determination and the time of the sample will be recorded. The amount and time of the last 3 doses taken prior to each PK sample will be recorded in the CRFs.

## 10.3 Primary and Secondary Data, Modeling, and Data Analysis

The pharmacology design will capture RAL trough concentrations from the first dose and out to steady-state. The data for each subject will be summarized statistically and used to determine if relationships exist between viral decay and drug exposure. These data may also be used for additional subsequent virologic or immunologic analyses completed to be completed by the study team.

## 10.4 Anticipated Outcomes

RAL has been shown to be exceptionally potent at lowering the initial viral load. This study design will allow us to collect the data needed to begin establishing relationships between RAL exposure and pharmacodynamic markers such as viral decay slope. RAL has considerable PK variability (~7-fold following multiple dosing), especially at the end of the dosing interval. Regardless, at doses of 100 to 600 mg twice daily, most subjects still achieved short-term viral load suppression. The primary explanation for this observation is that even at the lower dose, most subjects maintain trough concentrations at or above the IC95. RAL has minimal drug-drug interactions relative to PIs, but other drugs can still affect its concentration-time profile which will increase the PK variability. The drug is also a substrate for p-glycoprotein (P-gp), which could potentially be another source of increased variability when administered with P-gp inducers or inhibitors.

Given the potency of RAL at the doses studied, there is a possibility that no exposure-response relationships will be found (fixed effect). However, given the variability in exposure, one might be established. The goal of this study and subsequent analyses is NOT to develop guidelines for the use of therapeutic drug monitoring for RAL, but rather to establish a baseline drug exposure to which ensuing studies (especially drug interaction studies) can be compared to lessen the probability of treatment failure and development of resistance.

# 11.0 DATA COLLECTION AND MONITORING AND ADVERSE EVENT REPORTING

## 11.1 Records to Be Kept

CRFs will be provided for each subject. Subjects must not be identified by name on any CRFs. Subjects will be identified by the PID and SID provided by the ACTG DMC upon registration.

## 11.2 Role of Data Management

11.2.1 Instructions concerning the recording of study data on CRFs will be provided by the ACTG DMC. Each clinical research site is responsible for keying the data in a timely fashion.

11.2.2 It is the responsibility of the ACTG DMC to assure the quality of computerized data for each ACTG study. This role extends from protocol development to generation of the final study databases.

## 11.3 Clinical Site Monitoring and Record Availability

11.3.1 Site monitors under contract to the NIAID will visit participating clinical research sites to review the individual subject records, including consent forms, CRFs, supporting data, laboratory specimen records, and medical records (physicians’ progress notes, nurses’ notes, individuals’ hospital charts), to ensure protection of study subjects, compliance with the protocol, and accuracy and completeness of records. The monitors also will inspect sites’ regulatory files to ensure that regulatory requirements are being followed and sites’ pharmacies to review product storage and management.

- - 1. The site investigator will make study documents (e.g., consent forms, drug distribution forms, CRFs) and pertinent hospital or clinic records readily available for inspection by the local IRB, site monitors, FDA, NIAID, OHRP, and pharmaceutical supporter or designee for confirmation of the study data.

## 11.4 Adverse Event Reporting to DAIDS

The AEs that must be reported in an expedited fashion to the DAIDS RCC Safety Office are all Serious Adverse Events (SAE’s) as defined by International Conference on Harmonization (ICH) guidelines regardless of relationship to the study agent(s).

SAE’s as defined by ICH guidelines are: deaths, life-threatening events, events that require hospitalization or prolongation of hospitalization, events that result in persistent or significant disability or incapacity and congenital anomalies or birth defects. Important medical events as assessed by medical and scientific judgment may also be considered SAE’s by the investigator and should be reported in an expedited fashion.

The study agents for which relationship assessments are required are raltegravir (RAL, Isentress™) and emtricitabine/tenofovir disoproxil fumarate (FTC/TDF, Truvada®).

In addition to reporting all SAE’s as defined above, other events that sites must report in an expedited fashion include all cancers.

The DAIDS Table for Grading the Severity of Adult and Pediatric Adverse Events (DAIDS AE Grading Table), Version 1.0, December 2004, must be used and is available on the DAIDS RCC Web site: <http://rcc.tech-res.com/eae.htm>.

The timelines and mechanisms for reporting these events to the DAIDS RCC Safety Office are defined in the “Manual for Expedited Reporting of Adverse Events to DAIDS” (DAIDS EAE Manual), dated May 6, 2004. The DAIDS EAE Manual is available on the RCC Web site: <http://rcc.tech-res.com/eae.htm>. The DAIDS Expedited Adverse Event Reporting form (EAE Reporting Form), which should be used for reporting these events, is available on the RCC website: <http://rcc.tech-res.com/eae.htm>

The protocol-defined expedited event reporting period for this protocol is the entire study duration for an individual subject (from study enrollment until study completion or discontinuation of the subject from study participation for any reason).

After the end of the protocol-defined reporting period stated above, sites must report serious, unexpected, suspected adverse drug reactions if the study site staff becomes aware of the event on a passive basis, i.e., from publicly available information.

# 12.0 HUMAN SUBJECTS

## 12.1 IRB Review and Informed Consent

This protocol and the informed consent document (Appendix IV) and any subsequent modifications will be reviewed and approved by the IRB or ethics committee responsible for oversight of the study. A signed consent form will be obtained from the subject (or parent, legal guardian, or person with power of attorney for subjects who cannot consent for themselves). The consent form will describe the purpose of the study, the procedures to be followed, and the risks and benefits of participation. A copy of the consent form will be given to the subject, parent, or legal guardian, and this fact will be documented in the subject’s record.

